### Intervention group

The intervention will last 24 weeks and was developed based on the more promising BCTs for reducing sedentary behaviour in adults identified in a systematic review (27, 40) and based on previous effective interventions as described below. Participants will receive a standardised set of BCTs in the intervention (see Table – BCTs in intervention) but the strategies through which some BCTs are delivered will vary dependant on the optional behaviour change tool and mode of delivery selected (see Self-selected behaviour change tools below).

*This intervention is likely to be delivered and evaluated before society has returned to ‘normal’ after the COVID-19 pandemic. The proposed intervention is intended to be delivered remotely and thus requires little modification to make it appropriate for delivery during the pandemic. The online psychoeducation programme may be minimally changed to include discussion around barriers and ideas for reducing sitting under physical distancing conditions. The content of the health coaching sessions is also likely to be affected in the same way (i.e. discussion around reducing sitting in the context of pandemic restrictions) and this will be covered during training of the health coaches.*

#### Psychoeducation programme

After randomisation, all intervention participants will be provided with an online psychoeducation programme (can be accessed through a computer or via a smartphone i.e., mobile phone compatible). This programme is an adapted version of that used in our SMArT Work multicomponent intervention that led to significant and substantial reductions in workplace sitting after 12 months (48); this online psychoeducation programme is being used in the roll out of SMArT Work for free use by workplaces (https://www.smartworkandlife.co.uk/). The programme includes numerous interactive modules which will cover: 1) information on the health consequences of sitting too much (with a particular focus on diabetes), 2) benefits of reducing sitting, 3) participants reflect on their own sitting time, 4) goal setting for reducing sitting, 5) addressing potential barriers to behaviour change, And 6) the importance of self-monitoring and using prompts for behaviour change. At the end of the online programme, participants will indicate their choices with regards to the self-selected self-monitoring and prompt tools they would like to use and guidance documents for their use will be accessible from the online education programme portal.

#### Health coaching

Participants will then have a face-to-face health coaching session 1-3 days later (this will be done via video call or telephone if it cannot be done face-to-face) with a qualified health coach followed by telephone support at approximately 2, 6 and 12 weeks after baseline (it is expected participants will benefit most from more intensive support early in the intervention to help establish appropriate behaviour change strategies). A number of BCTs will be used within the health coaching sessions to include: goal setting, problem solving, action planning, review behaviour goals, discrepancy between current behaviour and goal, feedback on behaviour, self-monitoring of behaviour, social support-unspecified, information about antecedents, information about health consequences, prompts/cues, credible source, pros and cons, social reward, verbal persuasion about capability. The consultations will be semi-structured tailored sessions harnessed on the G.R.O.W (Goals, Reality, Options, Will) model (49) that will take each participant through the four stages to enhance intrinsic self-determined motivation, capability and opportunity. The initial session will focus on a discussion around Goals, Reality (barriers to reducing sitting), Options (self-selected behaviour change tools), and Will (confidence to change, how to action plan and monitor progress). Health coaches will use the content of the initial session to inform the subsequent telephone support calls. These telephone calls will involve reviewing behavioural goals, problem-solving and progress/adjustment of goals and how to achieve them. Participants will be able to contact health coaches via email/telephone outside of planned contact for additional social support if they wish (the frequency of which will be recorded). Where data can be shared between participant and health coach from the tools below, this will be used to inform health coaching sessions. Each of the health coaches will be trained by the research team to standardise the method of delivery and BCTs used during the intervention.

#### Self-selected behaviour change tools

Participants will select the behaviour change tools they would like to use for self-monitoring sitting time and prompting breaks in sitting. The use of tailored behaviour change strategies are more likely to lead to effective outcomes than fully prescribed strategies, as seen when delivering interventions using Motivational Interviewing (36, 37) and those based on Self-Determination Theory (38). In our experience with the STAND (50), SMArT Work (48), Beat the Seat (32) and other studies, we know that a one size fits all approach does not work. Thus, enabling participants to select their own tools within the same BCT strategy (e.g. self-monitoring of behaviour) may be a more effective approach to reducing sitting. Examples of self-monitoring and prompting tools can be seen in the table (Table - Overview of self-selection tools) and these were chosen as they draw from BCTs identified as being effective for reducing sitting in previous research. Each of these tools utilises strategies from the BCT taxonomy (51) and are commercially available other than the sitting diary that has been developed for this intervention. No matter what tool is chosen, the BCTs delivered from each tool, the psychoeducation programme and health coaching will combine to use the same BCTs.

These tools will be provided to participants (face-to-face or via post) or downloaded onto their phone/computer under guidance from the research assistant following completion of the online programme. Participants will be permitted to choose a maximum of one tool from each of these categories (e.g. one smartphone app, one computer prompt, one wearable device or paper-based tracker) but they are not required to choose a tool from every category. For example, a participant may choose a smartphone app and a wearable device only. The choice is theirs, thus making the intervention person-focused to increase potential effectiveness. This is consistent with Self-Determination Theory and accepted ways of boosting intrinsic motivation. The research assistant will provide a guidance document to the participant for each tool selected that will explain how to download and how it works. Participants will not receive any instructions on how often they should engage with the tools that they select given that the intervention is person-focused. The self-selected behaviour change tools used can be changed during the intervention period if a participant reports to the health coach or research team that they are not engaging with the tool. This might be due to reasons such as technical complexity, impracticality or a dislike of the tool. If there are any problems with using any of the tools during the intervention, participants will be able to contact the research assistant for troubleshooting.

### Control group

Participants randomised to this group will receive usual care. They will complete the same measurements as the intervention group. After the trial has concluded, they will be offered use of the psychoeducation programme and the self-selected behaviour change tools.

### Data collection

After eligibility screening, participants will be invited to complete baseline data collection, which will include demographic data (date of birth, sex, ethnicity, employment status, COVID-19 circumstances i.e. change to employment, social distancing or self-isolating). The below measures will be collected at baseline, 12 and 24 weeks. Participants will be required to fast for a minimum of 10 hours prior to each data collection session, which will take place at Brunel University London. At the end of each data collection session, participants will be provided with an activPAL activity monitor to wear for up to 8 days and will return this via post using a pre-paid envelope. All participants will receive a £10 amazon shopping gift voucher at each of the three data collection timepoints if they provide data and return the activity monitor to the research team.

**COVID-19 contingency:** If there are restrictions in place or advice from the government that people with Type 2 diabetes should continue to engage with physical distancing, data collection will take place remotely. Some of the measures will be removed, while some will be adapted so that the participants can perform and record these at home without the presence of a researcher. The nature of these changes or complete removal of the measure is explained for each measure proposed below. Participants will be provided with written and/or verbal guidance with regards to completion of each measure. Participants in this instance will not be required to fast overnight prior to data collection.

#### Sitting, standing and stepping

This will be measured using the activPAL device worn on the thigh for 24 hours/day for up to 8 days. The activPAL provides valid and reliable assessment of sitting, standing, stepping and postural transitions (52-56). Participants will record in a diary the time they woke up and got out of bed, time they went to bed, any times they worked, and to sleep and any periods when the device was removed. The following outcomes will be assessed: daily sitting time, time spent in prolonged sitting, the number of sit-upright transitions, standing time, stepping time, and light and MVPA steps. The device will be wrapped in a nitrile sleeve and waterproof dressing. The device is attached to the thigh using medical dressing. Participants will be asked to remove the activPAL when swimming in case it becomes detached and lost. Participants will receive a guidance document advising them on how to attach their activity monitor.

**COVID-19 contingency:** these activity monitors will be issued and returned by post, which is something we do regularly already in our research.

#### Body composition

This will be measured via body mass index (BMI), waist circumference and body fat% using bioelectrical impedance analysis. Height will be measured to the nearest 0.1 cm using a stadiometer (Seca 222, Seca Ltd, Birmingham, UK) with participants standing upright looking forwards, heels on the floor and feet together. Weight and body fat% will be measured using electronic weighing scales and bio-electrical impedance analysis (BIA) with the TANITA MC-780MA P segmental body composition analyzer (Tanita Corp., Tokyo, Japan). Participants will wear light clothing and remove shoes and socks for this measurement. This device produces valid and reliable body fat estimations in adults (57). BMI will be calculated as weight (kg) / height^2^ (cm). Waist circumference will be measured using an adjustable tape measure (Seca 201, Seca Ltd, Birmingham, UK) to the nearest 0.1 cm midway between the lowest rib and the iliac crest at the end of gentle expiration.

**COVID-19 contingency:** Participants will be asked to self-report their waist circumference at each relevant time point. They will be provided with a tape measure and written guidance on how to take this measure. Body fat %, height and weight measures will not be taken.

#### Cardiometabolic risk markers

Glycated haemoglobin will be measured using the Quo-Test HbA1c Analyzer (EKF Diagnostics, Cardiff, UK). Fasting total cholesterol, HDL, triglycerides and glucose will be measured using the CardioChek PA point-of-care-system (PTS Diagnostics, Indianapolis, Indiana). A finger prick sample technique will be used to collect capillary blood for these measures. Blood pressure will be measured on the right arm in a seated position using an Omron M5-I automatic monitoring device (Omron Matsusaka Co Ltd, Matsusaka, Japan). After 5 min of rest, the first reading will be taken with a further two readings taken with a 2 min rest between each. The average of the lowest two recordings will be used for analysis.

**COVID-19 contingency:** these measures will not be taken if it is not possible or safe to collect face-to-face data from participants.

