## RESEARCH OBJECTIVES

The main objectives of this feasibility study are to:

1. Establish and refine a recruitment strategy for people with Type 2 diabetes.
2. Determine participant attrition in the trial.
3. Determine completion rates for outcome measures (and whether these are sufficiently high to provide accurate data in a full trial).
4. Assess the acceptability of randomisation to the intervention and usual care.
5. Assess the acceptability of the intervention and data collection to participants.
6. Assess intervention fidelity and adherence.
7. Explore the feasibility of collecting data (as below) to inform the design of the health economics component in a full RCT.

The secondary objectives are to derive preliminary estimates of the effect of the intervention on participants’:

1. Device measured daily sitting time, prolonged sitting time, breaks from sitting and light and moderate-to-vigorous physical activity.
2. Cardiometabolic risk markers (BMI, waist circumference, body fat%, fasting glucose, glycated haemoglobin, lipids, blood pressure)
3. Fatigue, self-efficacy for reducing sitting time, psychological wellbeing, mood, physical functioning, musculoskeletal symptoms and quality of life.

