#### Physical function

This will be assessed using the Short Physical Performance Battery (SPPB) (68) and hand grip strength. The SPPB will be administered by trained researchers using standardised methods and includes assessment of standing balance, walking speed and rising from a chair. Standing balance will be tested using tandem, semi-tandem and side-by-side stands. For each stand type, the researcher will first demonstrate the task and will then support one arm while the participant positions their feet and then release support when the participant is ready and start timing. The timing is stopped when the feet move, the participant grasps the researcher for support or once 10 s has passed. For the semi-tandem stand, the heel of one foot (participant’s preference) is placed to the side of the first toe of the other foot. If unable to hold this position for 10 s, participants will be assessed with the feet in the side-by-side position. If the semi-tandem position is held for 10 s, participants will also be evaluated in the full tandem position with the heel of one foot directly in front of the toes of the other foot. Walking speed will be assessed using an 8-foot walking course with participants instructed to "walk to the other end of the course at your usual speed, just as if you were walking down the street to go to the store”. The walk is timed and is to be performed twice with the fastest used for analysis. For the chair stand (rising from a chair), a straight-backed chair will be placed next to a wall and participants will be instructed to fold their arms and stand up from the chair once. If they perform this successfully, the participants will be asked to stand up and sit down as quickly as possibly five times, which will be timed. Each of the SPPB assessments are scored on a 0-4 scale following published guidelines (68).

Grip strength will be measured on the dominant hand using a digital hand grip dynamometer (Takei Scientific Instruments Co.,Ltd, Yashorida, Japan) while in a standing position with the shoulder adducted and neutrally rotated and elbow in full extension. Three maximum attempts will be performed with a 1-min rest between each and the average recorded (69).

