#### Preliminary effects of the intervention

Descriptive statistics will be calculated to summarise the primary (device measured daily sitting time) and secondary outcomes (device measured prolonged sitting, breaks in sitting time, standing and stepping; body composition; cardiometabolic risk markers; psychological, sleep, musculoskeletal and wellbeing outcomes; physical function) and explore trends in the data. Continuous data will be summarised in terms of mean and standard deviation. Categorical data will be summarised in terms of frequency, counts and percentages. All baseline variables will be tabulated (no. (%), mean (SD)) by the treatment allocation and overall. Statistical analyses will be performed using SPSS v22 (IBM, Armonk, NY, USA).

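### Minor: the blood pressure rule selects readings by value and so reports levels biased low, and the BMI formula is written with height in centimetres

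*Protocol*

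**What the plan says.** Blood pressure (Protocol, Cardiometabolic risk markers): "After 5 min of rest, the first reading will be taken with a further two readings taken with a 2 min rest between each". The value carried forward is then defined: "The average of the lowest two recordings will be used for analysis". The section gives no reason for choosing by value.

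BMI (Protocol, Body composition): "Height will be measured to the nearest 0.1 cm using a stadiometer", and then "BMI will be calculated as weight (kg) / height^2^ (cm". No conversion to metres is stated there or elsewhere.

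Both measures appear under the secondary objectives, which seek preliminary effect estimates: "Cardiometabolic risk markers (BMI, waist circumference, body fat%, fasting glucose, glycated haemoglobin, lipids, blood pressure". The analysis is descriptive (Preliminary effects of the intervention): "Continuous data will be summarised in terms of mean and standard deviation".

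For grip strength, also measured three times, the Protocol uses every attempt (Physical function): "Three maximum attempts will be performed with a 1-min rest between each and the average recorded".

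Under the COVID-19 contingencies, blood pressure is dropped if face-to-face collection is not possible or safe, and height and weight are dropped when data are collected remotely.

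**The concern.** Discarding the highest of three readings is selection on the outcome itself. The mean of the lowest two can never exceed the mean of all three or the mean of any pair fixed in advance, so the direction of the error is certain. Its size depends on how much a participant's readings vary within a visit. The reported means by arm and visit would therefore sit below the pressure the readings estimate, by an amount that a reader of the tables cannot recover. If reading variability changed between visits, part of an apparent within-arm change would come from the rule.

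The BMI formula, applied literally to a height recorded in centimetres, does not give kg/m².

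At stake are the absolute levels of two secondary outcomes, and the measurement rules that a full trial might inherit from this one.

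**Working it through.** The Protocol gives no figure to reproduce here. It supplies the number and timing of readings, the selection rule, the BMI formula and the unit of height. The within-visit SD and any excess of the first reading over the later two are assumptions, shown as ranges.

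**1. Bias with exchangeable normal readings.** The expected maximum of three is 3/(2√π) = 0.846 SD above the true level μ. The three deviations sum to zero in expectation, so the other two average −0.846/2 = −0.423 SD.

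- SD 4 mmHg: 0.423 × 4 = 1.7 mmHg low
- SD 6 mmHg: 0.423 × 6 = 2.5 mmHg low
- SD 8 mmHg: 0.423 × 8 = 3.4 mmHg low

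**2. Bias when the first reading runs high (simulation).** Shift of the lowest-two mean from the settled level of readings 2 and 3, in mmHg:

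| First reading | SD 3 | SD 5 | SD 8 |
|---|---|---|---|
| +0 | −1.3 | −2.1 | −3.4 |
| +3 | −0.5 | −1.2 | −2.5 |
| +5 | −0.2 | −0.8 | −1.9 |
| +10 | −0.02 | −0.2 | −1.0 |

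The shift is always downwards and shrinks towards zero as the first reading becomes reliably the highest.

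**3. Variance within a visit.** The mean of all three has variance SD²/3 = 0.33 SD², and the mean of readings 2 and 3 has SD²/2 = 0.50 SD². The lowest-two rule has 0.39 SD² with exchangeable readings. This rises towards 0.50 SD² as the first reading is dropped more and more often.

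**4. Mean squared error around the settled level, SD 4.**

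- No first-reading effect: lowest two 0.39 × 16 + 1.69² = 9.1; readings 2 and 3, 0.50 × 16 = 8.0; all three, 16/3 = 5.3.
- First reading +3: lowest two 7.2 (simulated); readings 2 and 3, 8.0; all three, 16/3 + 1.0² = 6.3.

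The mean of all three is shifted upwards by one third of any first-reading excess: +1.0, +1.7 and +3.3 mmHg for an excess of 3, 5 and 10.

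**5. Between-arm difference, assumed true value −4 mmHg, exchangeable readings.**

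- Equal SD of 5 in both arms (simulated): −4.04 under the stated rule, −4.05 under the mean of three.
- SD 4 in the intervention arm and 6 in control: −4 + 0.423 × (6 − 4) = −3.15. Simulation gave −3.13, against −3.98 for the mean of three.

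**6. BMI.** For 85 kg and 170 cm, the formula as written gives 85/170² = 0.0029; in metres it is 85/1.70² = 29.4 kg/m². The ratio is 100² = 10,000 for every participant.

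**The case against.** The strongest reply on blood pressure is that the choice trades bias against variance. If the first reading runs 3 mmHg high, the stated rule has a smaller mean squared error than readings 2 and 3 (7.2 against 8.0 at SD 4, 17.0 against 18.0 at SD 6, 31.3 against 32.1 at SD 8). The mean of all three is then biased upwards by 1.0 mmHg, slightly more in size than the 0.85 mmHg downward bias of the stated rule at SD 4. This stands: neither replacement is better on every criterion. It does not justify selecting by value. An order-based rule uses the same readings, and the mean of all three has the lowest variance. A constant first-reading excess then acts as a constant, which cancels between arms, whereas the bias of the stated rule depends on variability.

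A reader might infer that the rule would create a spurious treatment effect. The documents do not support that. Both arms have the same measurements at the same visits, so steadier readings over time would affect both arms alike. Distortion needs variability that differs by arm, and nothing in the Protocol suggests it.

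A reader might also infer that reported BMI will be unusable. The formula is wrong as written, but values near 0.003 would hardly pass unnoticed into a table.

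Whether the lowest readings are chosen on systolic, on diastolic or separately for each is detail that a SAP could settle. Its absence is not counted against the Protocol.

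**Conclusion.** Both statements need correcting; the severity is minor. Blood pressure levels are biased low by 0.42 times the within-visit SD if readings are exchangeable, which is 1.7 to 3.4 mmHg for an assumed SD of 4 to 8. The bias is close to zero if the first reading is consistently well above the others. It largely cancels between arms unless within-visit variability differs by arm. These sizes rest on normally distributed readings and on SDs and offsets that the Protocol does not give; only the downward direction is certain without them. It would go too far to call the blood pressure values simply wrong: they are biased low.

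The BMI formula is wrong by exactly 10,000, but this is a unit correction. The feasibility objectives, the sample size and the device-measured sitting outcome are untouched, and under the COVID-19 contingency neither outcome is collected.

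**What to change.** **Cardiometabolic risk markers:** replace the selection by value with a rule set in advance by reading order, applied to the same readings for systolic and diastolic pressure. Either choice is defensible:

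- *Mean of all three readings.* Lowest variance (0.33 SD²). The cost is a level raised by one third of any first-reading excess, which cancels between arms if constant.
- *Mean of readings 2 and 3.* Unbiased for the settled level. The cost is variance of 0.50 SD², and so a higher mean squared error than the present rule when the first reading runs high.

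**Body composition:** state BMI as weight in kg divided by the square of height in metres, with the recorded height in cm divided by 100 first.

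The cost is one sentence each. No extra measurement is needed, since all three readings are already taken. Reported pressures will be somewhat higher than under the present rule.
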